### Participants/recruitment

The RCT will be conducted over a two-year period in a fertility clinic at a University hospital in the Netherlands. See Figure 1 for the flow chart of the study. The opt-in method will be used to recruit participants. In this method participants are sent an invitation to the trial and themselves contact the team to take part. The inclusion criteria will be all women undergoing a stimulated or cryopreserved IVF/ISCI treatment. The exclusion criteria will be women not speaking the Dutch language. All women meeting these criteria and starting a treatment will be sent a letter with general information about the study. Doctors and nurses working in the fertility clinic will remind women of the letter and the study. Patients who are interested in the study will return a reply form or e-mail indicating their interest and a researcher will contact them to give more information about the study and answer any questions. Those who decide to participate will be sent a written information sheet and a consent form to return in a pre-addressed stamped envelope. During their first visit to the hospital, more information will be given about the logistics of the study, as needed, but all patients will be given the same information according to a written protocol.

**Figure 1 F1:**
[figure not shown]
Flow chart study protocol.

The fourth group will be recruited as for the RCT. The fourth group will receive the same information as the participants from the RCT. Although this group will not be randomized, participants will be told that randomization will take place. Participants will be fully debriefed about the need for this deception at the end of the study.

The Ethical committee of the University of Utrecht provided ethical review and approval for this study, including the addition of the fourth non-randomized group (protocol number 10-174/K).

### Sample size

The sample size calculation for the three-arm RCT is based on the following parameters. To test the difference on anxiety between three groups using a mixed factorial ANOVA, power of 95%, α = 0.05 and a medium effect size a total of 297 subjects was required (99 patients per group) [24,25]. However, taking into account a 20% attrition rate at least 124 women will be recruited in each group. Effect size and attrition were derived from Lancastle and Boivin [1]. The addition of the fourth group only slightly modified sample size and 110 participants were recruited to the fourth group.

### Randomization

Stratified randomization of the 372 women into one of the three groups will be performed by using a computer-generated table of random numbers. The type of treatment (stimulated or cryopreserved IVF/ICSI) will stratify the population because emotions and expectations relative to a stimulated IVF/ICSI may differ from a cryo-preserved treatment [26,27]. Randomization will take place after the first assessment (Time 1 pre-intervention) between follicle aspiration and embryo transfer. An independent research nurse will be responsible for the randomization. Double blinding will take place for participants and clinic staff. Participants will not be told what intervention is being evaluated. The researcher will have no contact with participants after randomization. All women will receive written information about group assignment on the day of the embryo transfer. They will receive instructions for the waiting period in an opaque sealed envelope after the embryo transfer. The clinical staff that performs the embryo transfer will be blinded for the content of the envelope. After the embryo transfer, there will be no further contact between the clinical staff, other patients, or the researcher during the 14-day waiting period.

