### Intervention and control groups

Patients will be randomly assigned to one of the three groups: PRCI Intervention, Routine Care Control and Monitoring Control. In addition data will be collected for the PRCI Control.

The PRCI Intervention and PRCI Control groups will receive the PRCI. The PRCI is a small card that contains ten positive reappraisal statements and a leaflet with a detailed explanation about this coping approach. See Figure 2 for the PRCI card. Women will be instructed to read the PRCI at least twice a day, once in the morning and once in the evening as well as at any time they feel the need, and to think about how each statement applies to them personally. The other groups will not receive the PRCI. The Monitoring Control group will complete daily monitoring and questionnaires, whereas the Routine Care Control and PRCI Control groups will only complete questionnaires.

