## Discussion

Waiting for a potentially threatening medical test result in a period where there is no control in the outcome is very stressful and can bring about feelings of tension, nervousness and worry. The Positive Reappraisal Coping Intervention (PRCI) investigated in this RCT was specifically designed to help people cope with these medical waiting periods. Positive reappraisal coping is a set of strategies in which the significance of the event is reinterpreted in a more positive way [6]. In the present study, we will evaluate the effectiveness of the PRCI on psychological wellbeing of woman waiting for the results of an IVF/ICSI treatment cycle. Although the effectiveness of the PRCI has not yet been investigated, the coping literature shows that positive reappraisal strategies are one of the few ways of coping that are associated with increased positive affect and sustained ability to cope in unpredictable and uncontrollable stressor situations [6]. The results of this study could therefore be important because there is a lack of inexpensive self-help evidence based coping-interventions that could be used during the common medical waiting period.

This study has several strengths. This RCT was developed based on the results of several previous studies. The framework for developing complex interventions was used to design the PRCI and provide evidence of feasibility and acceptability in the studied population [1,35]. The MRC framework guides development to be theory based to create active components that can be delivered effectively during the RCT. Also the development and validation of the assessment tools was based on previous research showing good psychometric properties in Dutch translations for the key measures [1,9]. We chose a three-armed RCT to ensure balance between the determination of the general impacts of PRCI measured by questionnaires and its more specific impacts on the waiting period measured by monitoring. The Monitoring Control group of women who only monitor will allow us to disentangle effects due to PRCI and those due to monitoring per se on emotions and reactions during the waiting period. The RCT procedures match those of high quality trials with randomization and allocation concealment, blinding of patients and clinical staff [36].

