The decision to add the PRCI Control after the RCT has the disadvantage that this group will not be randomized. However, the group will allow us to estimate PRCI effects independent of daily monitoring, in case monitoring has an unexpected intervention effect that interacts with PRCI effects. Our RCT procedures use written protocols and blinding which should minimise the chance of systematic bias even in this non-randomized group with respect to attributes that may affect the dependent variables. The expected sample size will provide adequate power for detection of effects, determined from previous studies using the PRCI tool.

A limitation of this study is the method used for recruiting the participants. The opt-in method was employed to recruit on the advice of the Ethics Committee. In this method participants are sent an invitation to the trial and themselves contact the team to take part, which differs from the more conventional opt-out approach where all patients are contacted about the trial unless they have contacted the team to indicate that they do not wish to be approached. Although the opt-out method improves recruitment, the ethical committee often does not approve this method because repeated contact is too burdensome for participants [37,38]. In the study of Junghans at al. [37] there was a difference in risk factors between the two methods. Patients in the opt-in arm had fewer risk factors (44%) compared to patients in the opt-out arm (60%) (P = 0.053).

Another limitation could be the participation of only one hospital. We choose to recruit in only one hospital because this university hospital attracts patients from all over the country. However, as there is collaboration with other clinics nationwide inferences about the generalizability of findings can be determined via comparison of patient characteristics collected as part of wider collaborations.

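### The protocol article claims that participants are blinded, but women are told their group and can see whether they have the PRCI, and they then self-report the primary outcome

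*Protocol article*

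**What the plan says.** All references are to the protocol article.

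- **Randomization** states: "Double blinding will take place for participants and clinic staff". The sentence after it narrows this for participants: "Participants will not be told what intervention is being evaluated". For staff it says: "The clinical staff that performs the embryo transfer will be blinded for the content of the envelope".
- The same section then says: "All women will receive written information about group assignment on the day of the embryo transfer". Instructions for the waiting period follow in a sealed envelope after the transfer.
- **Intervention and control groups** describes what the PRCI women hold: "The PRCI is a small card that contains ten positive reappraisal statements and a leaflet with a detailed explanation about this coping approach". They are to read it at least twice daily. For the rest: "The other groups will not receive the PRCI".
- **Discussion**, on strengths: "The RCT procedures match those of high quality trials with randomization and allocation concealment, blinding of patients and clinical staff".
- **Discussion**, on the added fourth group: "Our RCT procedures use written protocols and blinding which should minimise the chance of systematic bias even in this non-randomized group". The sentence goes on to limit this to attributes that could influence the outcomes.

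**The concern.** A woman who has been told her group is not blinded to it. For many outcomes this would be a limited weakness, because someone else could assess the outcome blind. Here the woman is herself the assessor of HADS, FertiQoL, the WCQ and the daily record. Blinding of participants is therefore the masking that would protect the primary outcome, and the design does not have it.

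What is at stake is the reading of PRCI versus Routine Care. One group is given a coping method with an explanation of how it is meant to work, and the other is not. A difference in self-reported anxiety may then contain expectation or a wish to report benefit, as well as any effect of the PRCI. A reader or risk-of-bias assessor who accepts the stated double blinding would discount that possibility without grounds.

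**Working it through.** The point rests on no figure in the plan, so the check sets the statements side by side.

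1. **When does the woman learn her group?** Randomization takes place after the Time 1 assessment, between follicle aspiration and embryo transfer. Written notice comes on the day of transfer (Randomization).

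2. **Which assessments follow?** Table 1 gives HADS at Time 1 (hCG to embryo transfer), Time 2 (day 10 of the waiting period) and Time 3 (six weeks after transfer). Time 1 precedes allocation. Time 2 and Time 3 follow disclosure, so 2 of 3 HADS assessments are made with knowledge of the group. These are the two that carry any treatment effect.

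3. **Who makes the assessment?** Study measures lists self-report questionnaires, daily monitoring and medical records. The primary outcome and the secondary outcomes on emotions, depression, coping and quality of life are self-reported. Treatment outcome, taken from the chart, is the exception.

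4. **Could the materials mask the group even so?**
   - PRCI Intervention: card, leaflet, daily monitoring, and an intervention evaluation form at Time 2 (Table 1).
   - Monitoring Control: daily monitoring and questionnaires, no PRCI.
   - Routine Care: questionnaires only, no PRCI.
   - PRCI Control (non-randomized): card, leaflet and evaluation form, no daily monitoring.

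   The materials differ visibly between the groups. The Background reports that the earlier feasibility trial gave its controls ten control positive statements. No such material is described here.

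5. **What masking remains?**
   - Women are not told which intervention is being evaluated. That masks the study question, not the allocation. It is weak for a woman who holds a leaflet explaining a coping method and later fills in a form evaluating it. It may work better for Monitoring Control, who have a daily task of their own.
   - Staff performing the transfer do not know the envelope's content. Nothing in the document contradicts this.

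6. **Where is the claim relied on?** Twice in the Discussion: as a strength, and as part of the protection against systematic bias in the fourth group. That group also receives the card and leaflet, so its members are no more blinded to what they receive than the randomized PRCI group.

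**The case against.** The strongest defence is that the article qualifies its own claim at once: women do not know what is being tested, and that is real masking of the hypothesis. This stands in part. The document does not show what women are told about the other arms, and a woman in Monitoring Control may not see herself as a control. It is wrong to infer that there is no participant masking at all. The charge is that partial masking carries the wrong label.

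One could also read the written notice as describing the assignment procedure rather than naming the group. That is not the natural reading, and it would not rescue the claim, since the contents of the envelope show each woman what she has been given.

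Four further points limit how far the criticism goes.

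- **Staff blinding.** A reader might conclude that all the blinding claims fail. They do not. Transfer staff are masked, and there is no staff or researcher contact during the 14 days. Both guard against differential handling, although neither protects a self-reported score.
- **Routine Care.** These women do not get nothing. They receive the written notice, waiting-period instructions and reminders. They do not receive the PRCI.
- **The fourth group.** A reader might take the Discussion to claim that this group is unbiased. It says only that bias should be minimised with respect to attributes affecting the outcomes, and it admits the lack of randomization. Identical recruitment and information are relevant to that argument. Participant blinding to allocation is not available to support it.
- **Size.** It is tempting to put a false-positive rate on the problem. With 99 per group, no true effect and a two-sided 5% t-test, an assumed reporting shift of 0.1, 0.2 or 0.3 SD gives rejection in about 11%, 29% or 56% of trials. The arithmetic is right, but the shifts are invented and the planned analysis is a three-group repeated-measures ANOVA. The document supports neither a size nor a direction, so these figures carry no weight.

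**Conclusion.** The point holds as an incorrect statement about the design. Participants are described as blinded, while the article's own procedures disclose the group and make it visible. The conclusion rests on the article's wording and on the absence of any described sham or comparison material for the controls.

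It reaches the primary outcome at both post-randomization assessments and every self-reported secondary outcome. How much bias follows, and in which direction, cannot be determined from the document, and the verdict does not depend on it. Nor does the document show that the eventual report will draw a wrong conclusion. What it does show is that PRCI versus Routine Care on self-reported outcomes cannot be presented as protected by participant blinding. The comparison with Monitoring Control may be less exposed because those women have an active task, but this is an inference: the article chose that arm to deal with reactivity to monitoring, not expectation.

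**What to change.** - **Randomization:** replace the double-blinding sentence with a statement that allocation is concealed until the day of embryo transfer; that staff performing the transfer are blinded to the envelope's content; and that participants, who assess the outcomes themselves, are not blinded to allocation and are only not told which intervention is under evaluation.
- **Discussion, strengths:** delete blinding of patients. Keep allocation concealment and staff blinding.
- **Discussion, fourth group:** do not cite participant blinding as protection against systematic bias. Rely only on identical recruitment, identical information and written protocols.
- **Discussion, limitations:** state that PRCI versus Routine Care on self-reported outcomes cannot separate the effect of the PRCI from expectation or reporting effects, and that this may be only partly reduced in the comparison with Monitoring Control.

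The cost is a few sentences and a less favourable account of the trial's quality. No arm, outcome, sample size or analysis changes.

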### Intervention and control groups

Patients will be randomly assigned to one of the three groups: PRCI Intervention, Routine Care Control and Monitoring Control. In addition data will be collected for the PRCI Control.

The PRCI Intervention and PRCI Control groups will receive the PRCI. The PRCI is a small card that contains ten positive reappraisal statements and a leaflet with a detailed explanation about this coping approach. See Figure 2 for the PRCI card. Women will be instructed to read the PRCI at least twice a day, once in the morning and once in the evening as well as at any time they feel the need, and to think about how each statement applies to them personally. The other groups will not receive the PRCI. The Monitoring Control group will complete daily monitoring and questionnaires, whereas the Routine Care Control and PRCI Control groups will only complete questionnaires.

**Figure 2 F2:**
[figure not shown]
**PRCI intervention.** © 2008 by Cardiff University. All rights reserved. No part of this document may be reproduced or transmitted in any form or by any means, electronic, mechanical, photocopying, recording, or otherwise, without prior written permission of authors.

### Objective

The aim of this study is to investigate the effect of the PRCI on psychological well-being of women waiting for the results of an IVF/ICST treatment. The primary outcome is level of general anxiety measured before the waiting period (pre-intervention), on day ten of the 14-day waiting period (intervention) and six weeks after the start of the waiting period (post-intervention). Secondary outcomes are positive and negative treatment emotions during the waiting period, depression, coping style, quality of life and treatment outcome.

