A cycle of in vitro fertilisation typically requires nine to 12 days of self-injection with potent fertility drugs to stimulate the production of oocytes (eggs), retrieval of oocytes via trans-vaginal ultrasonography, fertilisation of oocytes in the laboratory with partner or donor sperm, and transfer of the resulting embryo to the uterus. Couples then wait two weeks to find out whether implantation and a pregnancy have occurred. Women often report that IVF/ICSI is an emotional and physical burden that can cause anxiety and stress [8,9]. The aspects most frequently reported as stressful are the fourteen-day waiting period between embryo transfer and the pregnancy test, and being informed that the treatment was unsuccessful [8-12]. Symptoms of anxiety and depression have been shown to increase during the waiting period after ET [1,2,10,11]. The lack of control the patient has to influence outcome during this period has also been shown to contribute to the increase in distress [2].

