## Methods/Design

The PRCI will be evaluated in a three-arm Randomized Controlled Trial (RCT). Participants will be randomized to an intervention, monitoring control group or routine care. To capture the general impact of the PRCI all three groups will complete questionnaires at three time points: just before the waiting period (Time 1: pre-intervention), on Day 10 of the 14-day waiting period (Time 2: intervention) and 6 weeks after the start of the waiting period (Time 3: post-intervention). Table 1. Mobile phone text reminders will be sent to patients about completing the Time 1 and Time 3 questionnaires (if necessary) and all patients will receive a reminder just prior to the Time 2 assessment on the ninth day of the waiting period.

**Table 1 T1:** Measurement timetable according to group

**Measurements**	**T1 hCG to Embryo transfer**	**T2 Day 10 waiting period**	**T3 Six weeks after ET**
**BIF**	1,2,3,4	------	------
**HADS**	1,2,3,4	1,2,3,4	1,2,3,4
**FertiQol**	1,2,3,4	1,2,3,4 (Treatment only)	1,2,3,4 (non-pregnant group only)
**WCQ**	1,2,3,4	1,2,3,4	1,2,3,4
**DRK one day**	1,2,3,4	3,4	------
**IEF**	------	1,4	------
**DRK daily**	------	1,2	------
**Medical chart review**	------	------	1,2,3,4

Note. Numbers refer to group: 1 = PRCI Intervention, 2 = Monitoring Control, 3 = Routine Care and 4 = PRCI Control (non-randomized). BIF = Background Information Form, HADS = Hamilton Anxiety and Depression Scale, FertiQol = The Fertility Quality of Life, WCQ = Ways of Coping Questionnaire, DRK = Daily Record Keeping, IEF = Intervention evaluation form.

To capture the specific impacts of PRCI on the waiting period the intervention group will rate daily their emotions and reactions during the 14-day waiting period. Daily monitoring has previously been shown to be an efficient and sensitive way of evaluating emotional reactions during fertility treatment [2,9] and to be sensitive to intervention effects during ART [22]. One potential drawback of this method of assessment is that it may impact on the reporting of emotions itself. For example, habituation or sensitisation to monitoring per se may decrease or increase reporting of anxiety compared to groups that do not monitor [23]. Due to this potential reactivity the monitoring control group will also monitor emotions and reactions daily during the waiting period. The routine care control group will not receive the intervention or monitor reactions.

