### Statistical analysis

IBM SPSS Statistics will be used to perform the statistical analysis. Equivalence of baseline measures between groups will be examined by one-way analyses of variance (ANOVA) for normally distributed variables on interval or ratio level, chi-square for normally distributed variables on nominal level and Kruskal Wallis *H* test for normally distributed variables on ordinal level. If study variables are not normally distributed then data will be transformed to normalise (e.g., square root, log, etc. as is required). If the groups are not comparable on demographics, medical history or gynaecological variables, those variables will be employed as covariates in subsequent analyses. To examine the differences between groups over time a repeated measure mixed factorial ANOVA design will be used for variables on interval or ratio level. To compare the fourth group with the three separate groups also an ANOVA design will be used. Intention to treat and multi-level modelling will be used to analyse the data to take account of attrition.

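### The primary outcome spans three visits with no primary time point or deciding F test named, and pre-randomisation anxiety is a level of the outcome when it could be a covariate

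*Protocol article*

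**What the plan says.** The Objective section of the protocol article defines the primary outcome across three visits: "The primary outcome is level of general anxiety measured before the waiting period (pre-intervention), on day ten of the 14-day waiting period (intervention". The third visit comes at six weeks, counted from when the wait starts. No visit is singled out.

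The Randomization section fixes the order of T1 and allocation: "Randomization will take place after the first assessment (Time 1 pre-intervention) between follicle aspiration and embryo transfer". The Background says of the period after transfer: "Couples then wait two weeks to find out whether implantation and a pregnancy have occurred". T3 at six weeks is therefore about four weeks after the result. Table 1 itself splits T3 by outcome: FertiQoL is given to "1,2,3,4 (non-pregnant group only", while HADS is given to every group at all three visits.

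For analysis, the Statistical analysis section says: "To examine the differences between groups over time a repeated measure mixed factorial ANOVA design will be used". Its covariate rule admits only demographic, medical-history and gynaecological variables on which the groups turn out to differ. Baseline HADS anxiety is not among them. The section ends by naming intention to treat and multi-level modelling as the way to handle attrition, without further detail.

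The Sample size section asks for 95% power at alpha 0.05 and a medium effect, in a mixed factorial ANOVA of three groups. It arrives at 297 women (99 per group), raised to 124 per group for 20% attrition.

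**The concern.** A three-group, three-visit mixed ANOVA yields two tests that could be called the primary result: a group main effect, averaged over visits, and a group-by-time interaction. They answer different questions and can disagree on the same data.

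Neither directly estimates the effect of the intervention during the wait. T1 carries no treatment effect, because it precedes allocation. At T3 the women already know whether they are pregnant. The stated aim concerns women who are waiting, and only day 10 meets that description.

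Two things are at stake. Depending on the F test that is read, a real day-10 effect could be missed. A significant primary result could also arise when day 10 shows nothing. In addition, T1 anxiety is collected from every group but is not planned as a covariate, which would sharpen the day-10 comparison.

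**Working it through.** **Inputs from the article.** Three groups, 99 evaluable per group (N = 297), alpha 0.05, power 95%, medium effect, attrition 20%.

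**Assumptions, since the article gives no SD, correlation or numerical effect.** Medium means Cohen f = 0.25. Visits have equal variance and a common correlation r. Only the PRCI arm is shifted: by d SD at T2, by c × d at T3, and by 0 at T1.

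**Step 1: which test reproduces 297?** Noncentral F, f = 0.25, power 0.95:
- 4-df group-by-time interaction, noncentrality f² × N: N = 300 (error df 2(N − 3)) or 302 (nine-cell factorial). At N = 297 the first version gives power 0.948.
- One-way three-group ANOVA: N = 252.
- Between-group main effect over three visits, r = 0.5: N = 168.
- Interaction with noncentrality f² × N × 3/(1 − r), r = 0.5: N = 54.

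Of these conventions, only the first comes close to 297. The attrition step is exact: 99/0.8 = 123.75, so 124 per group and 3 × 124 = 372.

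**Step 2: noncentrality for a day-10-only effect (c = 0).** One shifted arm out of three gives a between-group sum of squares of (2/3)d² at T2.
- Main effect (2 and 294 df): the averaged shift is d/3, and the variance of a three-visit mean is (1 + 2r)/3. λ = 99 × (2/3)(d/3)² / [(1 + 2r)/3].
- Interaction (4 and 588 df): λ = 99 × (2/3)(2/3)d² / (1 − r).
- T1-adjusted T2 test (2 and 293 df): λ = 99 × (2/3)d² / (1 − r²).

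At d = 0.5 and r = 0.5:
- Main effect: 66 × 0.02778 / 0.6667 = 2.75, power 0.30.
- Interaction: 44 × 0.25 / 0.5 = 22.0, power 0.98.
- Adjusted T2: 66 × 0.25 / 0.75 = 22.0, power 0.99.

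The interaction and the adjusted test have equal λ here. The adjusted test gains because it spends 2 df, not 4.

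**Step 3: the range.**

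| d | r | T3 share c | Main effect | Interaction | T1-adjusted T2 |
|---|---|---|---|---|---|
| 0.5 | 0.4 | 0 | 0.32 | 0.95 | 0.98 |
| 0.5 | 0.5 | 0 | 0.30 | 0.98 | 0.99 |
| 0.5 | 0.6 | 0 | 0.27 | 0.99 | >0.99 |
| 0.5 | 0.5 | 0.5 | 0.59 | 0.92 | 0.99 |
| 0.5 | 0.5 | 1 | 0.85 | 0.98 | 0.99 |
| 0.3 | 0.5 | 0 | 0.13 | 0.60 | 0.71 |
| 0.3 | 0.5 | 0.5 | 0.25 | 0.46 | 0.71 |
| 0.3 | 0.5 | 1 | 0.41 | 0.60 | 0.71 |

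**Step 4: specificity.** The interaction treats the visits symmetrically. Put 0.5 SD at T3 and nothing at T2, and λ is unchanged: 44 × 0.25/(1 − r) = 18.3, 22.0 and 27.5 for r = 0.4, 0.5 and 0.6. Power is again 0.95-0.99. The adjusted T2 test would stay at its 5% error rate in that case.

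**The case against.** The tempting stronger reading is that the mixed ANOVA dilutes the waiting-period effect and leaves the trial with about 30% power. The documents do not support it. Differences between groups over time is ordinary wording for the interaction, and the interaction is the only convention tried that comes near 297. The Sample size section's phrase about a difference between three groups does not single out the main effect, since a mixed factorial design contains both tests. A reader might also infer that the two sections contradict each other. They do not; they leave the choice open.

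Three further points deserve weight.
- Comparing change across visits with baseline as a level is valid in a randomised trial. Adjusting for baseline is an efficiency gain and corrects no bias.
- T3 is deliberate. The Methods/Design section uses the questionnaires for general impact and daily monitoring for the waiting period itself, and the Hypotheses section speaks of effects across assessments. Pregnancy status adds variance at T3, but under randomisation it creates no group difference if the intervention does nothing.
- Model detail is often left to an analysis plan, which is not shown here.

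The first two points stand, and they make demoting T3 more debatable than adjusting for T1. The third stands only in part: the article itself fixes the three-visit outcome, names the model and restricts the covariates. A follow-up contrast by visit would help to interpret a significant interaction, but none is described and it would not be the primary test.

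**Conclusion.** The concern holds in a limited form. The article names neither a primary visit nor a deciding test, and it keeps a pre-randomisation measurement as a level of the primary outcome.

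If the main effect decides, a 0.5 SD effect confined to day 10 has power of only 0.27-0.32. If the interaction decides, which is the likelier intention, power for that effect is 0.95-0.99, against 0.98 to above 0.99 for the T1-adjusted test, so the loss is small. It grows when the effect is half maintained at T3 (0.92 against 0.99 at 0.5 SD, r = 0.5) or smaller (0.46-0.60 against 0.71 at 0.3 SD, r = 0.5).

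The more lasting weakness is interpretation: a significant interaction does not show which visit or which arm differs, and T3 alone can produce it. All power figures rest on the assumed effect, correlation and equal-variance structure. This is a should-fix, not a must-fix.

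**What to change.** Use the multi-level model that the Statistical analysis section already mentions. Take HADS anxiety at T2 and T3 as outcomes and T1 HADS anxiety as a covariate, with group, time and group-by-time terms. Make the T1-adjusted group difference at T2 the primary estimate, tested first by the three-arm 2-df test. Follow it with PRCI Intervention against Monitoring Control and PRCI Intervention against Routine Care, under a stated multiplicity rule. Report the T3 difference separately as persistence.

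No new data are needed. There are three costs. T3 no longer contributes to the primary test, although the hypotheses span all assessments. The pairwise step has less power than the 2-df test: with Bonferroni at 0.025 each, a contrast has about 0.57 at 0.3 SD and r = 0.5. Finally, the article shows that recruitment has begun, so the change must be dated and documented in the registration.
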